## Abstract

**Background:**

Family caregivers play a vital, yet stressful role in managing the healthcare needs and optimizing the quality of life of patients with advanced cancer, from the time they are newly diagnosed until end of life. While early telehealth palliative care has been found to effectively support family caregivers, little work has focused on historically under-resourced populations, particularly African American and rural-dwelling individuals. To address this need, we developed and are currently testing Project ENABLE (*E*ducate, *N*urture, *A*dvise, *B*efore *L*ife *E*nds) Cornerstone, a lay navigator-led, early palliative care coaching intervention for family caregivers of African American and rural-dwelling patients with newly diagnosed advanced cancer.

**Methods:**

This is a 2-site, single-blind, hybrid type I implementation-effectiveness trial of the Cornerstone intervention versus usual care. Cornerstone is a multicomponent intervention based on Pearlin’s Stress-Health Process Model where African American and/or rural-dwelling family caregivers of patients with newly diagnosed advanced cancer (target sample size = 294 dyads) are paired with a lay navigator coach and receive a series of six, brief 20–60-min telehealth sessions focused on stress management and coping, caregiving skills, getting help, self-care, and preparing for the future/advance care planning. Subsequent to core sessions, caregivers receive monthly follow-up indefinitely until the patient’s death. Caregiver and patient outcomes are collected at baseline and every 12 weeks until the patient’s death (primary outcome: caregiver distress at 24 weeks; secondary outcomes: caregiver: quality of life and burden; patient: distress, quality of life, and healthcare utilization). Implementation costs and the intervention cost effectiveness are also being evaluated.

**Discussion:**

Should this intervention demonstrate efficacy, it would yield an implementation-ready model of early palliative care support for under-resourced family caregivers. A key design principle that has centrally informed the Cornerstone intervention is that every caregiving situation is unique and each caregiver faces distinct challenges that cannot be addressed using a one-size-fits all approach. Hence, Cornerstone employs culturally savvy lay navigator coaches who are trained to establish a strong, therapeutic alliance with participants and tailor their coaching to a diverse range of individual circumstances.

**Trial registration:**

ClinicalTrials.gov NCT04318886. Registered on 20 March, 2020.

**Supplementary Information:**

The online version contains supplementary material available at 10.1186/s13063-022-06305-w.

## Background

Many of the 2.8 million family caregivers (FCGs) of persons with advanced cancer are historically under-resourced [1], particularly African Americans and rural-dwelling individuals [2]. Both African American and rural-dwelling caregivers report less paid and unpaid assistance with providing day-to-day care and higher hours of care, including more hours providing transportation, advocating for patient needs, and completing medical and nursing tasks [2]. Many have poor access and awareness of formal support services and receive no formal training [1, 3–7]. This is concerning in an advanced cancer context where FCGs provide complex care and support, including managing and monitoring symptoms, coordinating care and communication among multiple specialist providers, managing medications and breathing treatments, giving emotional, spiritual, and companionship support, and providing end of life care [6, 8]. Providing this complex care in combination with coping with a close friend or family member having advanced cancer can be extraordinarily stressful, particularly as individuals approach end of life [9–11]. Patients receiving support from distressed and unprepared FCGs may result in suboptimal home care leading to poorer patient quality of life and increased healthcare utilization [12–14].

Hence, there is a critical need to develop and test interventions for African American and rural-dwelling FCGs [15, 16]. Reports from National Cancer Institute and National Institute of Nursing Research caregiving summits [17, 18], systematic reviews [15, 16, 19], and the National Academy of Medicine [20] have detailed major limitations of existing cancer caregiver interventions, including a lack of attention towards under-resourced populations, unknown implementation costs, questionable scalability, over-reliance on highly trained professionals (e.g., nurses, psychologists, behavioral therapists), lengthy sessions over a short duration, and lack of demonstrated impact on patient outcomes and healthcare utilization. Recognizing these priority areas, we developed and successfully piloted ENABLE (*E*ducate, *N*urture, *A*dvise, *B*efore *L*ife *E*nds) Cornerstone, a lay navigator-led, telehealth-based early palliative care intervention for rural and African American caregivers of patients with newly diagnosed advanced cancer [21, 22]. Building upon our prior trials and community stakeholder formative evaluation work [5, 12, 23–28], this multicomponent intervention is based on Pearlin’s Stress-Health Process Model [29] and consists of a series of six weekly semi-structured coaching sessions and long-term, monthly follow-up until the patient’s death and into bereavement. Lay navigators, overseen by an interdisciplinary outpatient palliative care team, employ health coaching techniques and caregiver distress screening to behaviorally activate and reinforce coaching on managing stress and coping, getting, and asking for help, improving caregiving skills, and decision-making/advance care planning during brief in-person/telephonic sessions plus monthly follow-up from diagnosis through early bereavement [21].

The original ENABLE early palliative care caregiver intervention was tested in a New England population of advanced cancer caregivers [23, 24]. While these results showed that intervention group caregivers had lower depressive symptoms and stress burden, the trial sample included nearly all white individuals and the intervention was led by advanced practice nurse coaches. To adapt this early palliative care intervention to a more historically under-resourced and racially diverse population and leverage a more available workforce, we completed a qualitative formative evaluation study with caregivers and patients of rural and minority populations in the Southern U.S. employing lay oncology navigators [28]. After eliciting and incorporating participant feedback, a new version of the ENABLE Caregiver intervention was developed called ENABLE Cornerstone. ENABLE Cornerstone was subsequently evaluated for feasibility, acceptability, and potential efficacy in a small-scale, pilot randomized trial (intervention vs. usual care) with 63 African American and/or rural-dwelling FCGs (November 2019 to March 2021) [22]. This pilot demonstrated high acceptability and data collection completion rates. In addition, the preliminary efficacy scores for mitigating distress were promising for both Cornerstone caregiver participants and their care recipients. Hence, we are now conducting a fully powered randomized trial of the Cornerstone intervention. This manuscript describes the conceptual foundations of Cornerstone and the clinical trial design.

## Methods and design

### Study aims and hypotheses

The first aim of this hybrid type I randomized implementation-effectiveness trial is to test the effect of ENABLE Cornerstone on FCG outcomes over 24 weeks [30, 31]. Our primary hypothesis is that compared to usual care, intervention group caregivers will report lower distress as measured by the Hospital Anxiety and Depression Scale (HADS) over 24 weeks [32, 33]. Our secondary hypotheses are that compared to usual care, intervention group participants will report better quality of life (QOL) (PROMIS Global Health 10) and lower caregiver burden (Montgomery-Borgatta Burden Scale) over 24 weeks. The second aim is to test the effect of ENABLE Cornerstone on patient outcomes. We hypothesize that compared to usual care, patients of caregivers randomized to receive Cornerstone will report lower distress (HADS), better QOL (PROMIS Global Health 10), and lower healthcare utilization over 24 weeks [34, 35]. For our third aim, we are evaluating implementation costs and the cost effectiveness of Cornerstone implementation on caregiver and patient outcomes, including healthcare utilization. Finally, we have an exploratory aim to analyze mediators and moderators (e.g., resilience, social support effectiveness, preparedness) of the relationship between the intervention and caregiver and patient outcomes.

### Overview of the study design

This is a 2-site, single-blind, hybrid type I randomized implementation-effectiveness trial comparing the ENABLE Cornerstone intervention to usual care. The target sample is 294 caregivers and 294 of their African American and/or rural-dwelling care recipients with newly diagnosed advanced stage cancer (see Fig. 1). Half of the caregiver participants (*n* = 147) are being randomized to the ENABLE Cornerstone intervention, which is led by a specially trained lay navigator coach and consists of a series of 6 weekly semi-structured coaching sessions and monthly follow-up. The other half of the participants (*n* = 147) are assigned to usual care. Blinded assessments are completed by mailed paper-and-pencil questionnaires at baseline and every 12 weeks until the patient’s death or the study ends. The research protocol was approved by the University of Alabama at Birmingham (UAB) Institutional Review Board (IRB) (#300005045) and the WCG IRB (#20201135) (commercial IRB). The trial is registered as NCT04318886 on clinicaltrials.gov. The study protocol uses the SPIRIT reporting guidelines [36].

**Fig. 1 Fig1:**
[figure not shown]
Hybrid type I randomized effectiveness-implementation trial design

### Setting and eligibility criteria

Participants are being recruited from oncology outpatient clinics at two sites: the O’Neal Comprehensive Cancer Center at UAB in Birmingham, Alabama, and the USA Health Mitchell Cancer Institute (MCI) at the University of South Alabama (USA) in Mobile, Alabama.

For FCGs, inclusion criteria are (1) 21 years of age or older; (2) self-endorsing or identified by the patient as “an unpaid spouse/partner, relative, or friend who knows them well and who provides regular support due to their cancer and who does not have to live in the same dwelling”; (3) caring for a patient with an advanced stage cancer; (4) English-speaking; and (5) able to complete baseline measures. Caregiver participants are not required to have an agreeable patient willing to participate in the study. Exclusion criteria include self-reported active severe mental illness (i.e., schizophrenia, bipolar disorder, major depressive disorder), dementia, active suicidal ideation, uncorrected hearing loss, or active substance abuse.

Patients are invited but not required to participate in the trial for data collection purposes only. Patient inclusion criteria are (1) 21 years of age or older; (2) diagnosed within the past 60 days of initial screening with an advanced cancer, defined as metastatic and/or recurrent or progressive stage III/IV cancer, including brain, lung, breast, gynecologic, head and neck, gastrointestinal, genitourinary cancer, and hematologic malignancies; (3) English-speaking; and (4) able to complete baseline measures. Exclusion criteria include (1) receiving hospice and (2) medical record documentation or self-report of active severe mental illness (i.e., schizophrenia, bipolar disorder, or major depressive disorder), dementia, active suicidal ideation, uncorrected hearing loss, or active substance abuse.

### Recruitment

Our recruitment approach is clinic-based but executed remotely. Research coordinators access the electronic medical record and screen for initial patient eligibility by reviewing the outpatient clinic schedules of partnering oncologists. All patients with a planned office visit in the upcoming 1 to 2 weeks are reviewed for eligibility. For patients appearing to meet eligibility criteria, an opt-out email is sent to the patient’s oncologist, which informs them that the individual will be approached for participation in the study and to reply to the email only if they do not want the patient approached. In our pilot trial [22], recruiters initially approached patients and their FCGs in-person prior to their appointment in the waiting room to introduce the study and invite eligible and agreeable individuals to participate. However, COVID-19 forced us to shift from in-person recruitment to a remote approach. For the rest of our pilot trial and for this current trial, study coordinators mail a study flyer and an opt-out letter the day of the patient’s clinic appointment (arriving at their home a few days later) to introduce the study and let them know that a member of the research team will be contacting them by phone to discuss the study. Individuals are given a number to call if they do not wish to be contacted further for the study. A recruiter then calls the participants by phone to introduce the study, assess eligibility, and invite them to participate. Participants are consented verbally via an IRB approved waiver of *signed* informed consent (caregiver and patient consent form templates available upon request). Consented participants are immediately mailed a copy of the informed consent document for their keeping and a paper-and-pencil baseline survey to complete and return by mail. Once the study team receives these completed baseline surveys in the mail, the caregiver and patient (if participating) are randomized. See Fig. 2 for a SPIRIT figure.

**Fig. 2 Fig2:**
[figure not shown]
SPIRIT figure of study enrollment, interventions, and assessments

### Randomization and blinding

Randomization occurs at the level of the caregiver participant, with participating patients assigned to the same group as their caregiver. The randomization scheme is executed via REDCap (Research Electronic Data Capture) [37], a secure web-based software platform designed to support randomization and data capture for research studies. Participants are randomly assigned (1:1) using a computer-generated program overseen by the trial statistician. The randomization scheme is stratified by site (UAB and MCI) and blocked within strata (using random block lengths 4 and 10). After randomizing a FCG in REDCap and if selected for the Cornerstone program, the assigned lay navigator informs them by phone of their group assignment and introduces the intervention activities. If randomized to the usual care group, the program manager notifies FCGs by mail of their group assignment. All other members of the research team, including the principal investigator (PI) and all co-investigators, are blind to group assignment and participants are instructed to not discuss their assignment with study staff. The allocation sequence will remain concealed until the last participant completes 24-week data collection and the data have been checked for completeness and accuracy.

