#### Discontinuation of study intervention

Participants may withdraw from the study or voluntarily stop intervention sessions at any time. Reasons for discontinuing the intervention are documented (e.g., too burdensome, too busy, patient too ill), though the participant is invited to continue with data collection. The PI can also discontinue a participant from the study for the following reasons: (1) significant study intervention non-adherence, (2) lost to follow-up, or (3) occurrence of an event, medical condition, or situation such that continued collection of study data would not be in the best interest of the participant.

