10	Monthly follow-up, bereavement, and suicide protocol	Learn how to check in with family caregivers monthly, provide condolences and support after a patient’s death, and act if a family member or patient expresses a desire to harm themself or others.

Throughout the study, lay navigator coaches engage in weekly supervisory meetings with the PI (a board-certified palliative care advanced practice nurse [[name]]) and a nurse practitioner co-investigator ([name]) to review calls and sessions with all active intervention group participants, including adverse events. In addition, coaches have 24/7 access to the PI for any acute participant issues that arise.

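### The protocol says the PI and all co-investigators are blind, yet the PI and one co-investigator review active Cornerstone participants every week, and that PI can remove participants from the study

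*Protocol article*

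**What the plan says.** The Randomization and blinding section describes two roles that know the allocation: the lay navigator, who phones caregivers assigned to Cornerstone, and the program manager, who writes to those assigned to usual care. It then closes the list: "All other members of the research team, including the principal investigator (PI) and all co-investigators, are blind to group assignment". It adds: "The allocation sequence will remain concealed until the last participant completes 24-week data collection", and until those data have been checked.

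Interventionist training and oversight says that, throughout the study, "lay navigator coaches engage in weekly supervisory meetings with the PI" and "a nurse practitioner co-investigator". The purpose of the meetings is "to review calls and sessions with all active intervention group participants, including adverse events". Between meetings, "coaches have 24/7 access to the PI for any acute participant issues that arise".

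Discontinuation of study intervention says that caregivers who stop the sessions are invited to go on providing data. It then says: "The PI can also discontinue a participant from the study". Three reasons are listed, and the first is marked non-adherence to the intervention.

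Safety monitoring committee names the PI, with the IRB and the committee, as monitoring how timely and how good the data are.

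**The concern.** Two sections make statements about the same people that cannot both be true. One says the PI and every co-investigator are blind. The other gives the PI and a co-investigator a standing weekly task that discloses assignment.

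Two things are at stake. The first is reporting. The trial is labelled single-blind, and a results paper that repeats the blinding sentence would claim a protection that the design does not have. The second is conduct. The PI holds at least one decision that blinding is meant to protect, namely whether a participant leaves the study and so stops contributing outcomes. If that decision is taken with knowledge of arm, missing 24-week data can differ between arms for reasons that stem from the decision-maker. That would weaken the intention-to-treat comparison promised for Aims 1 and 2.

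**Working it through.** There is no figure to reproduce. The check is whether the sections can all hold together.

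1. **Who is exempt from blinding.** Randomization and blinding names the lay navigator and the program manager as the people who tell caregivers their group. Everyone else is declared blind, and the PI and all co-investigators are named explicitly. No exception is made for supervision.

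2. **What the supervisors see.** The weekly meetings cover calls and sessions with active intervention-arm participants. Usual-care caregivers have no coach, calls or sessions of this kind. Anyone discussed is therefore in the Cornerstone arm by definition.

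3. **Could the review be anonymous?** The article does not say that cases are reviewed without identifiers. The round-the-clock route to the PI for acute problems would be hard to run without knowing who the participant is.

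4. **Result of steps 1 to 3.** The PI and the nurse practitioner co-investigator know the assignment of the Cornerstone participants they review. For these participants, concealment from the PI ends when they first come up for review, long before the 24-week data are complete and checked.

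5. **What the PI decides.** The PI may discontinue a participant from the study, which is wider than stopping the sessions. The first listed reason, non-adherence to the intervention, can apply only in the Cornerstone arm, because usual care has no sessions to adhere to. So an unblinded decision-maker holds a removal criterion that exists in one arm only.

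6. **Against the other commitments.** If removal from the study ends data collection, removal for non-adherence works against the intention-to-treat approach in the Statistical analysis plan section. It also sits poorly with the same discontinuation section, which invites those who stop the sessions to stay in data collection.

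7. **Data monitoring.** The PI shares the monitoring of data timeliness and quality. Separately, the data are to be checked for completeness and accuracy before allocation is revealed. The article does not say who does that check, so nothing ensures that it is done blind.

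**The case against.** The strongest reply is that the practical effect is small. The primary outcome is a mailed caregiver questionnaire, and coordinators enter de-identified responses twice. The PI is not described as collecting, entering or analysing outcomes. Data monitoring is shared with the IRB and with a committee whose co-chairs are independent. Close clinical supervision of lay coaches is a sensible arrangement and is not at fault. All of this stands. It limits the size of the problem but does not make the blinding sentence true.

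Several stronger readings are tempting, and the article does not support them:

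- **The PI knows the arm of all 294 caregivers, 147 by review and 294 − 147 = 147 by exclusion.** This needs a full enrolment roster in the PI's hands, which the article does not mention. Only active participants are reviewed, so a Cornerstone caregiver who stopped or never started may also go undiscussed. Absence from the meetings does not prove usual care.
- **The fidelity rater breaks the blind too.** The rater is an unnamed study team member and could be one of the exempt roles. Overseeing a coach's retraining need not disclose any participant's assignment either.
- **The phrase "Blinded assessments are completed by mailed paper-and-pencil questionnaires" is false.** It can mean that staff handle the forms blind. The article openly says that caregivers are told their group, so it does not claim blind respondents. The phrase deserves clarification only.
- **Adverse-event counts by arm will not be comparable.** The article describes neither the capture of adverse events in usual care nor a planned comparison by arm.
- **The PI controls covariate choice, extreme values or database lock.** No section gives the PI these powers.

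One practical objection also stands. A blinded person cannot apply a criterion of non-adherence to the intervention, because doing so reveals the arm. The fix has to allow for that.

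**Conclusion.** The point holds as an internal contradiction with a concrete consequence. At least two people whom the protocol declares blind, the PI and the supervising nurse practitioner co-investigator, know the assignment of the Cornerstone participants they review. One of them can end a participant's time in the study, on grounds that include one applicable to a single arm.

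This rests on one assumption: that cases are discussed in a form that identifies the participant. The article does not say otherwise, and on-call escalation makes it likely. The further step, that removal from the study ends outcome collection, follows from the plain meaning of the words.

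No size of bias can be calculated, since the article gives no rate of removals by the PI. The likely route is differential missing data, with little scope for direct influence on questionnaire scores. The correction should be made because the statement is wrong, it would carry into the trial report, and it is cheap to put right.

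**What to change.** Reconcile the sections on blinding, discontinuation and oversight as follows.

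- **Blinding statement.** List the coaches, the program manager, the PI and the supervising co-investigator as unblinded, with the fidelity rater if that person is not already in an exempt role. Limit the blinding claim to the staff who really are blind, and name their roles.
- **Outcome assessment.** State that outcomes are self-reported by caregivers who know their assignment. If blinded assessment refers to staff handling of the forms, say so.
- **Ending data collection.** Separate stopping the intervention from leaving the study. Keep caregivers who stop the sessions in data collection, as the discontinuation section already invites, so that non-adherence does not by itself end follow-up. Have existing team members who are blind to arm make the remaining decisions that end outcome data collection, on information that does not reveal the group.
- **Data checks.** State that the completeness and accuracy checks before allocation is revealed are done by blinded staff. The trial statistician oversees the randomization program, so that person's blinding should be stated before the task is assigned there.

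The PI's supervision of the coaches and on-call role can continue unchanged. The cost is a wording amendment and a reassignment of a few tasks among existing staff, with no change to the sample size, the assessments or the intervention.
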